### Cohort

All participants in the cohort receive usual multidisciplinary COPD care including guideline-directed physical therapy. In the Netherlands usual COPD care is given by a pulmonologist and/or a GP. This usual COPD care entails lung function testing, medication prescription for COPD and counselling, including education about the disease, symptoms and risks and tailor-made advice, which basically comes down to two major aspects; stop smoking and increase physical activity in everyday life [41]. In the light of the latter, all patients in the cohort are referred for usual physical therapy and physical activity advice. Usual physical therapy in the Netherlands is guideline-directed physical therapy (gdPT), provided by registered physical therapists and based on the KNFG physical therapy guidelines for COPD [35]. These guidelines provides assistance for applying physical therapy intervention (diagnosis and treatment) in COPD patients coping with impairments in mucus clearance, pulmonary function, muscle function and exercise capacity, and with limited physical activities due to dyspnoea or exercise intolerance. In the guidelines the effectiveness of several treatment modalities (specifically exercise training, breathing exercises, peripheral and respiratory muscle training) was reported and evidence based recommendations for the application of these modalities in physical therapy programmes were made. Moreover, disease management strategies are integrated. Short term goals incorporate improvement of patient’s knowledge, self-management and confidence to accomplish activities. Medium term goals are relief of dyspnoea, improvement of impaired airway (mucus) clearance, and improving or retaining exercise performance and physical activity in everyday life [35]. Long term goals entail improvement or preservation of disease related quality of life. Physical therapists are free to compile a patient-centred program at one’s professional discretion, within the limitations of the guideline. Hence, frequency of the guideline-directed physical therapy for COPD in the Netherlands varies; patients visit their physical therapist generally one to three times a week, for one hour, ranging from one-time consultation to multiple consultations during 3–12 months, depending on disease severity (based on usual care given in participating physical therapy practices) (Table 1).

**Table 1 T1:** Contrasts between RCT experimental and control group and cohort

	** *Intervention* **	** *Content* **	** *Intensity* **	** *Frequency* **	** *Start* **
Cohort	**Guideline-directed physical therapy (gdPT):**	One or more of:	Ranging on the full intensity scale	On average:	
		Exercise training, peripheral muscle strength training, respiratory muscle training, breathing exercises, electrical muscle stimulation, physical activity in daily life (homework)		30 minutes to 1 hour	
	A programme made by individual PTs, within the limitations of the KNFG physical therapy guideline for COPD (usual care)				
				1 to 3 times a week	
				During 3 months to multiple years	
RCT experimental group	**Protocol-directed physical therapy (pdPT):**	Both exercise training and peripheral muscle strength training;	Endurance/ interval training ≥ 60% of (sub) maximum, muscle strength training ≥ 80% of maximum, always: borg-scale ≥5	Minimal:	*Early* PT: starting within 56 days after an acute exacerbation
				1 hour	
	A complete programme by protocol, according to the KNGF physical therapy guideline for COPD, but with strict conditions			Twice a week	
		When indicated: respiratory muscle training, breathing exercises, electrical muscle stimulation		During 12 months	
		Always: physical activity in daily life (homework)			
RCT control group	**Sham-treatment (ST):**	One-time consultation: advice to be physically active in daily life			
	No physical therapy				
	*Or*				
				Maximal:	
	Very low-intensity exercise training	Exercise training only	Endurance/ interval training ≤ 15% of (sub) maximum or borg-scale ≤2	30 minutes	
				Once a week	
				During 12 months	

Definition of abbreviations: RCT = randomised controlled trail; COPD = chronic obstructive pulmonary disease; KNGF = the Dutch Society for Physical Therapy.

### Randomised controlled trial

As patients enter the RCT, after experiencing a COPD exacerbation, they may be assigned to either the experimental group or control group. Contrasts between the experimental group, control group and the cohort, based on content, intensity, frequency and timing, are displayed in Table 1.

#### *Experimental group*

Patients in the experimental group receive protocol-directed physical therapy (pdPT). The content of the pdPT is based on the on the KNGF physical therapy guidelines for COPD, like the guideline-directed physical therapy in the cohort [35]. However, in the RCT the physical therapy follows a strict protocol. The therapy specifically concerns *early* physical therapy, starting within 56 days after an acute COPD exacerbation. Patients in the experimental group receive a programme of one hour, twice a week for one year. The programme includes high-intensity exercise training, which entails endurance and/or interval training with an intensity of 60% or higher of (sub) maximum physical exertion, based on the results of a maximal cardiopulmonary exercise test (CPET) and six-minute walk test. In addition, ratings of perceived exertion and dyspnoea of five or higher on the modified Borg-scale (0–10) are used to tailor exercise intensity [42]. Peripheral muscle strength training is provided (a programme combining upper and lower extremities) with an intensity of 80% or higher of maximum physical exertion, based on the results of one-repetition maximum tests or handheld dynamometer measurements. Again, ratings of perceived exertion and dyspnoea of five or higher on the modified Borg-scale are used to adjust exercise intensity [9]. When indicated, the programme includes respiratory muscle training, breathing exercises and electrical muscle stimulation. In addition, much emphasis is given to the assessment and treatment of physical inactivity in daily life. Patients are asked to increase their total physical activity on their own. At least 30 minutes of moderately intense physical activity on at least five days a week is the current recommended level. All visits for treatment and all advice for home training are part of standard procedure, following the KNGF guideline physical therapy for COPD and the Dutch Standard for Healthy Exercise (NNGB) [35,43]. An additional file shows the intervention in more detail according to a framework based on the International Classification of Functioning, Disability and Health (ICF) [see Additional file 1] [44].

#### *Control group*

Patients in the control group receive sham-treatment (ST), which entails no or very low-intensity exercise training, for one year. The latter applies only if the participant in the control group insists on training in a physical therapy practice. The very low-intensity exercise training is limited to a maximum of 30 minutes once a week, with an intensity of 15% or lower of (sub) maximum physical exertion, based on the results of a maximal CPET and six-minute walk test. In addition, ratings of perceived exertion and dyspnoea of two or lower on the modified Borg-scale (0–10) are used to tailor exercise intensity [42]. There will be no further peripheral muscle strength training, respiratory muscle training, breathing exercises nor electrical muscle stimulation [35]. Furthermore, patients will be advised to do at least 30 minutes moderately intense physical activity on their own for at least five days a week according to the physical activity norm [43].

### Physical therapists

All interventions are carried out in primary care physical therapy practices. Registered physical therapists, experienced in COPD care, who are willing to participate in the study, will be recruited through local physical therapy networks in the Netherlands that already have mapped the specialised skills of these health professionals and registered who treats a sufficient number of patients with COPD (with a minimum of 5–10 per week).

Therapists will be invited to attend information/training sessions given by the research group and related COPD experts. Information will be given about the aim and content of the cohort and RCT along with information about the necessary clinical measurements. Lectures will be given on the latest information on COPD and updates on the current COPD guidelines and on counselling (in line with the Dutch college of general practitioners (NHG) standard COPD). Furthermore, a COPD master class will be given to the network of participating physical therapists in cooperation with the Dutch Paramedical Institute (NPi).

### Data collection

Participants will be monitored by physical therapists with the help of a high quality electronic patient record system that is COPD-specific and serves simultaneously as a research database for the experimental group as well as for the control group. Moreover, the system will be used by physical therapists as guidance for treatment of the experimental group, since the KNGF guidelines physical therapy for COPD is fully incorporated within this system (for example: an alert will be visible on the computer screen when a patient’s performance is below 80% of the predicted peripheral muscle strength or when FEV_1_ <50% and Medical Research Council dyspnoea score (MRC) ≥2 an advice to initiate multidisciplinary evaluation and rehabilitation is given).

Primary and secondary study-specific outcome measures will be assessed with the help of the COPD-specific record system. In addition, the system will contain information about the content of physical therapy, the duration of physical therapy, the total amount of physical therapy sessions, the duration per session, and the adherence to physical therapy.

#### *Primary outcome measure*

The primary outcome measure will be exacerbation frequency, calculated as the number of COPD exacerbations experienced by the patient in a post exacerbation period of two years. A COPD exacerbation will be identified as a sustained worsening of the patient’s condition occurs from the stable state and beyond normal day-to-day variations that is acute in onset and may warrant additional treatment [45]. A recurrent exacerbation will be defined as a subsequent occurrence; exacerbations are assumed to be independent of each other. The follow-up period is twelve months (twenty-four months for the long-term outcome measurement) to overcome time confounding, since exacerbation frequency is seasonal and particularly related to influenza and other viral epidemics [45].

In the cohort, exacerbations will be identified by means of an event based approach, whereas in the RCT exacerbations will be identified by means of an event based approach (health care contact) and symptom based approach (clear increase of respiratory symptoms). Usual assessment of exacerbations is done by recording health care contacts. However, there are many underreported exacerbations in COPD patients when using this event based method [46]. On average, these underreported exacerbations have similar severities to reported exacerbations [45]. Therefore, increase of respiratory symptoms will also be recorded in the RCT. When measuring the appearance of exacerbations with these two methods, this trial is able to compare event based and symptoms based methods in relation to the primary and some of the secondary outcome measures.

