**Figure 3 F3:**
[figure not shown]
**Planning of outcome measurements in the RCT.** The diary cards are not included in the Figure, but they are used by the patient every day of every month until T_6_. In the cohort, the baseline measurement is followed by the same measurements as on T_3_ in the RCT and are repeated every three months for at least twelve consecutive months. Definition of abbreviations: T_0_ = baseline measurement; T_1_ – T_10_ = consecutive measurements in time after the baseline measurement; A = Anthropometric measures; B = Bicycle test results (maximal cardiopulmonary exercise test (CPET)); S = Spirometry results; 6 = 6MWT + Borg score and mGUG + Borg; M = peripheral muscle strength; P = physical activity in daily life with accelerometer; Q = CCQ*, CRQ-SR, EQ-5D*, DS14, MRC and level of effective mucus clearance, level of motivation, physical activity, physical therapy compliance*; C = questionnaire to assess direct and indirect costs; and G = Global Perceived Effect*. Measurement occasions are explained in the Table above the Figure. *The only measurements on T_1_ and T_2_.

In the RCT, prospective daily diary cards are distributed every month for twenty-four consecutive months and are returned by the patient at the end of every month. The retrospective questionnaire on the use of health care is send to the patient once every three months for twenty-four consecutive months.

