### Project time frame

The project in total will take five years. During the first three years of the project, physical therapy practices and COPD patients will be recruited. Patients in the cohort will be followed at least until the end of the project. Patients included in the RCT will be followed for two years by means of the COPD-specific electronic patient record system, while the treatment will be one year. The last year of the project is reserved for the processing and analysis of data, as well as the publication of results.

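### The primary exacerbation count has two conflicting windows (24 and 12 months), and the diary schedule and project timetable do not secure the two-year count for every patient

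*Protocol article*

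**What the plan says.** **Window.** The section Primary outcome measure counts "the number of COPD exacerbations experienced by the patient in a post exacerbation period of two years". Three sentences later it states: "The follow-up period is twelve months (twenty-four months for the long-term outcome measurement", giving seasonality as the reason. Size of the study population assumes a 12-month intervention and 24 months of follow-up. Data analysis, Clinical effectiveness, evaluates exacerbations at 12 and at 24 months and calls neither primary.

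**Diaries.** The Figure 3 legend says of the diary cards that "they are used by the patient every day of every month until T_6". The text under the same figure says "prospective daily diary cards are distributed every month for twenty-four consecutive months".

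**Timetable.** Project time frame gives the project five years in total and each RCT patient two years of follow-up, with one year of treatment. It also says "During the first three years of the project, physical therapy practices and COPD patients will be recruited" and "The last year of the project is reserved for the processing and analysis of data".

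**The concern.** The time window is part of the definition of a count endpoint, and here the protocol gives it two values. The choice matters because treatment ends at month 12: a 12-month count covers the treated year only, whereas a 24-month count adds a year off treatment. The two results can differ. With no window named, the primary time point could be settled after both are known.

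The diary end point matters for the same reason. Symptom-based exacerbations are defined from the daily diary. Event-based ones are found through diaries and through missed therapy appointments. Scheduled treatment stops at month 12, and control patients may have no appointments at all, so the diary carries most weight in year two. That is the year for which the legend appears to drop it.

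The timetable bears on whether patients recruited late can supply a second year before analysis begins.

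**Working it through.** **1. Where T6 falls.** The legend states "T_1_ – T_10_ = consecutive measurements in time after the baseline measurement". The RCT visits are at 3 and 6 weeks and at 3, 6, 12 and 24 months, and the cost questionnaire is three-monthly for 24 months. Two early visits plus eight three-monthly occasions make ten: 3 weeks, 6 weeks, then 3, 6, 9, 12, 15, 18, 21 and 24 months. On that numbering T6 is month 12 and T10 is month 24. This is an inference, because the table in the figure is not shown.

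**2. Timetable.** Three years + two years + one year = 6 years, against 5 stated. A patient entering at month 36 reaches 24 months at month 60, so up to 12 months of follow-up overlap the reserved year.

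Suppose that data close at month 48 and RCT entry ends at month 36. Follow-up is then min(24, 48 − entry month): 24 months for entry by month 24, falling to 12 months for entry at month 36. Late entrants average (24 + 12)/2 = 18 months. Entry is assumed uniform:

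| RCT entry period | Share reaching 24 months | Mean follow-up (months) | Share of planned person-time |
|---|---|---|---|
| months 0–36 | 24/36 = 67% | 24 × 0.667 + 18 × 0.333 = 22.0 | 22.0/24 = 92% |
| months 6–36 | 18/30 = 60% | 24 × 0.6 + 18 × 0.4 = 21.6 | 90% |
| months 12–36 | 12/24 = 50% | 24 × 0.5 + 18 × 0.5 = 21.0 | 87.5% |

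If follow-up runs to month 60 instead, everyone reaches 24 months, but the last visit falls at project end.

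**3. The plan's sample size.** The drop-out step reproduces: 79/0.8 = 98.75, so 99, against 100 stated. The 79 itself cannot be verified, because no control rate is given and the 22% is not said to be relative or absolute. Two readings can both yield 79:

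- *Relative 22%, Poisson counts.* n = (1.960 + 0.842)² × (1 + 0.78) / (0.22² × μ) = 288.7/μ, where μ is the mean count per control patient. Setting n = 79 gives μ = 3.65, or about 1.83 per year over 24 months.
- *Absolute 22 points, two proportions.* For example, 0.54 against 0.32 gives 79.

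**4. Power under the Poisson reading.** Calibrate to 80% at 79 per group over 24 months. If a fraction f of the events is observed and the relative effect stays constant, power = Φ(2.802 × √f − 1.960).

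- f = 22/24: 2.802 × 0.957 − 1.960 = 0.722, so about 76%.
- f = 0.5 (12 months only): 2.802 × 0.707 − 1.960 = 0.021, so about 51%.

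On this calibration, restoring 80% at 12 months needs 2 × 79 = 158 per group, or 158/0.8 = 197.5, so 198 with drop-out.

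**The case against.** The strongest reply is that the article clearly intends 24 months. It schedules a 24-month visit, promises each RCT patient two years, assumes 24 months in the sample size and distributes diaries for 24 months. Against this stand one sentence in the outcome section and one figure legend. Reserving year 5 for analysis does not forbid data collection then, and cohort patients are expressly followed to the end of the project. This much stands: the intention is recognisable, and the timetable defect is an overlap rather than a certain loss of data. It does not settle which window is primary, since the outcome section itself labels 24 months the long-term measurement.

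Several stronger readings are tempting, but the documents do not support them.

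- *The plan delivers data only to 12 months.* It assures 12 months for all if data close at month 48; most patients, or at least half under the entry patterns above, would still reach 24.
- *About 107 completers (200 × 0.667 × 0.8) against the 158 required.* This counts late recruits as contributing nothing, although each supplies 12 to 24 months to a count model.
- *Two-year power of 27%.* This needs the effect to vanish completely after month 12 (overall reduction 11%) on top of the unverified Poisson calibration. With a half-size effect in year two (16.5% overall), the same model gives about 54%. The article says nothing on persistence.
- *The count starts up to 56 days before randomisation.* The phrase about a post-exacerbation period could be read so, but the Abstract times follow-up from inclusion, and nothing starts counting earlier.
- *T6 is certainly month 12.* The planning text lists six post-baseline visits, the sixth at month 24, so the alternative exists. It would leave T7 to T10 with no scheduled occasion.
- *Year two would have no data without diaries.* Therapist symptom notes and the three-monthly questionnaires remain, though neither is a daily prospective record.

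**Conclusion.** The point holds as an internal contradiction that should be resolved before analysis. The primary window has two values in one paragraph, and neither the sample size section nor the analysis section resolves them. The diary end has two statements under one figure, and the stated periods add up to six years in a five-year project.

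The consequence for the data is moderate. If collection closes at month 48, 12 months is the longest period complete for everyone. Under uniform entry from month 0, about 67% reach 24 months (50% if RCT entry starts at month 12), about 92% of person-time is obtained, and power falls from 80% to about 76%. These figures assume uniform entry ending at month 36. The power figures also assume a constant relative 22% Poisson effect, which the article does not confirm. The main risk is an unfixed primary time point, more than lost person-time.

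**What to change.** 1. In Primary outcome measure and in Data analysis, name one primary window, counted from randomisation, and make the other secondary. Which one is for the sponsor to decide.
2. Correct the Figure 3 legend so that diaries run to month 24 (T10 on the inferred numbering). Both windows then have the same data source.
3. In Project time frame, either let RCT follow-up run into year 5 and restate the analysis period, or close at month 48 and analyse the 24-month count with a person-time offset and administrative censoring.
4. Restate the sample size for the chosen window, giving the control rate and saying whether the 22% is relative or absolute.

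**Cost.** Items 1 and 2 are wording. Keeping 24 months as primary either shortens the analysis year or gives up a small share of person-time (about 8% under uniform entry from month 0). Choosing 12 months fits the timetable and the treatment period. However, if 79 per group was based on 24 months of events, stated power falls to about 51% on the Poisson calibration, and 80% would need about 198 per group with drop-out.

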### The impact of COPD exacerbations

The definition of COPD by the Global Initiative for Chronic Obstructive Lung Disease (GOLD) explicitly mentions COPD exacerbations as an enormous burden for patients [1] and health care systems [6]. Exacerbations are defined as “an event in the natural course of the disease characterised by an increase in dyspnoea, cough and/or sputum beyond normal day-to-day variations. The onset is seemingly acute and may require a change in regular medication or hospitalisation” [1,7]. They are mostly precipitated by an infectious systemic inflammation of the upper respiratory tract and the tracheobronchial tree [1].

Since exacerbations are a significant cause of morbidity (e.g. acute muscle deconditioning and muscle weakness), hospital admissions, impaired health status, impaired quality of life and even death in patients [8-10], prevention is indicated. A relatively small percentage of patients (10%) experiencing frequent exacerbations account for over 70% of all medical costs due to COPD [6]. A study of Pitta et al. (2006) showed that COPD patients tend to be severely inactive during and after an exacerbation; which is worrying since there seems to be a strong association between physical inactivity in patients who recently exacerbated and an elevated risk of (re)hospitalisation due to a COPD exacerbation [11,12]. It appears that patients with recurrent exacerbations show a more rapid decline in their physical activity level than stable patients and their functional capacity gradually decreases faster over time [11]. Besides, their more pronounced skeletal muscle weakness and decreased six-minute walk distance (6MWD, a measure of functional exercise capacity), are risk factors for future exacerbations and higher mortality [9,13]. Consequently, unstable patients, who frequently experience exacerbations, enter a downward spiral of inactivity and exacerbations. Hence, adequate management of exacerbation (prevention) in patients is considered worldwide as one of the main goals in controlling COPD [1].

Although medical treatment modalities for COPD have improved, there is still no pharmacological therapy available that reduces the progression of the disease [4]. Though, patients with COPD, irrespective of disease stage, have shown to benefit from exercise programmes [12] resulting in improved exercise performance and health status [4,5,14-17].

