### Size of the study population

For the cohort study 300 patients with COPD will be recruited. This number is based on the calculated sample size for the RCT part of the study. The sample size calculation for this RCT is based on the identification of a minimal relevant clinical difference in exacerbation frequency between the experimental and the control group. The difference in exacerbation rate is expected to be 22% (based on exacerbation rates found in previous studies with rehabilitation programmes) [37,38]. The probability that the study will detect a treatment difference is 80% at a two-sided 5% significance level. This is based on the assumption that the intervention period will be 12 months, the follow-up period will be 24 months and the ratio control subjects to intervention subjects is 1:1. A sample size calculation for comparing event rates between two independent groups is used, resulting in 79 participants per group [39,40]. Assuming outcome data will be analysed prospectively and considering a drop-out rate of 20%, 100 patients per group will be needed in this two treatment parallel-design study.

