### Data analysis

#### *Clinical effectiveness*

The descriptive characteristics are presented quantitatively as mean (±standard deviation) or median (5^th^ - 95^th^ percentile), depending on the data distribution, whenever the variable is continuous or as a percentage whenever the variable is dichotomous or categorical. Data will be analysed with SPSS-19. Assumptions accompanying the following statistical methods will be checked and all data analyses will be applied by a blinded analyst.

Data from the RCT will be analysed to examine intervention main effect on the counts for the primary outcome (exacerbation frequency) and the secondary outcomes. All exacerbations from each patient will be used as the dependent outcome to evaluate the effect of physical therapy at the end of the intervention (12 months) and follow-up (24 months). Measurement moments for secondary outcomes are baseline, three and six weeks, three, six, twelve and twenty-four weeks. The effects of the variable of primary interest, physical therapy (pdPT), will be analysed in a generalized linear model (GLM) for group (intervention vs. control) analysis of covariance with adapted regression for count data distribution. Analyses of secondary outcomes will be done with linear regression analysis and generalized linear models. Since exacerbation outcome in the RCT is measured with two methods, analyses will be based on the event-based approach, on the symptom-based approach and on a combination of both. Potential confounding by variables like, age, gender, GOLD stage, smoking, physical activity in daily life, exacerbation history, severity of latest exacerbation, and comorbidity, will be controlled for. Results from a ‘per-protocol’ and an ‘intention-to-treat’ principle will be compared. At a minimal statistical power of 80%, p-values smaller than 0.05 will be considered as significant.

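### The protocol assumes repeat exacerbations are independent, and its sample size shows no allowance for variation between patients; if 79 per group is a Poisson figure, power for the primary count is well below 80%

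*Protocol article*

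**What the plan says.** All references are to the protocol article.

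- *Primary outcome measure*: the outcome is a count of exacerbations per patient over two years. A recurrent exacerbation is any later occurrence, and "exacerbations are assumed to be independent of each other".
- *Size of the study population*: "The difference in exacerbation rate is expected to be 22" per cent, "based on exacerbation rates found in previous studies with rehabilitation programmes". "The probability that the study will detect a treatment difference is 80% at a two-sided 5% significance level". Allocation is 1:1, with 12 months of intervention and 24 months of follow-up. "A sample size calculation for comparing event rates between two independent groups is used, resulting in 79 participants per group"; a 20% drop-out allowance raises this to 100. The section gives no control rate or dispersion and does not say whether 22% is relative or absolute.
- *Clinical effectiveness*: "All exacerbations from each patient will be used as the dependent outcome", at 12 and 24 months, in a generalized linear model with a regression adapted to count data. Model assumptions will be checked, and exacerbation history is among the variables to be controlled for. No count distribution is named.
- *The impact of COPD exacerbations*: "A relatively small percentage of patients (10%) experiencing frequent exacerbations account for over 70% of all medical costs due to COPD". The same section says that unstable patients enter a self-reinforcing decline of inactivity and further exacerbations.

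**The concern.** Several exacerbations in one patient are not independent pieces of information if patients differ in their underlying rate, or if one episode raises the risk of the next. The background describes both. Counts then vary more between patients than a Poisson distribution allows, and each further event from the same patient adds less information than an event from a new patient.

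Two things are at stake. First, a sample size that ignores this variation overstates power, and a null result could be misread as evidence of no effect from a trial with 80% power. Second, if the assumption were carried into the analysis model, standard errors would be too small and a chance difference could be declared significant. The first concerns what the protocol states. The second depends on a modelling choice that it leaves open.

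**Working it through.** **Inputs from the document:** two-sided 5% (z = 1.96), 80% power (z = 0.84), so (1.96 + 0.84)² ≈ 7.85; 22% difference; 1:1 allocation; 79 per group.

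**Assumptions:** the control mean per patient, m1 (not stated); 22% read as relative, so rate ratio RR = 0.78 and m2 = 0.78·m1; negative binomial dispersion k (not stated), shown at 0.2, 0.5 and 1.0. With k = 0 the model is Poisson.

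**Step 1. Reproduce 79.** There is no unique reproduction.

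- *Poisson, 22% relative:* n = 7.85 × (1/m1 + 1/m2) / (ln 0.78)², with (ln 0.78)² = 0.0617. At m1 = 3.65: 7.85 × (0.274 + 0.351) / 0.0617 = 79.5. So 79 needs about 3.65 control events per patient, for example 1.83 a year for 24 months.
- *Two proportions, 22 points absolute, pooled formula:* 0.60 against 0.38 gives 79.9; 0.54 against 0.32 gives 78.3, which rounds up to 79. Control proportions of about 0.52 to 0.70 all give 78 to 80.
- *Poisson, absolute difference of 0.22 a year:* 79 at a control rate of about 0.35 a year over 12 months, or 0.60 a year over 24 months.
- *Negative binomial, 22% relative:* k = 0.1 with 5.4 control events also gives 79.

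The drop-out step is consistent: 79/0.8 = 98.75, stated as 100.

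**Step 2. Power at 79 per group on the relative Poisson route.** SE² = (1/m1 + 1/m2 + 2k)/79 and power = Φ(|ln 0.78|/SE − 1.96), with |ln 0.78| = 0.2485 and m1 = 3.65. The number per group for 80% power is n = 7.85 × (1/m1 + 1/m2 + 2k)/0.0617.

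| k | SE | 0.2485/SE | Power | n per group for 80% | Reduction detectable at 79 |
|---|---|---|---|---|---|
| 0 | 0.089 | 2.79 | 80% | 79 | 22% |
| 0.2 | 0.114 | 2.18 | 59% | about 130 | 27–28% |
| 0.5 | 0.143 | 1.73 | 41% | about 207 | 33–34% |
| 1.0 | 0.182 | 1.36 | 28% | about 334 | 40–41% |

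The ranges in the last column reflect whether the variance is held at RR = 0.78 or re-solved at the detectable ratio.

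**Step 3. Could a higher control rate rescue 79?** As m1 grows without limit, n tends to 7.85 × 2k/0.0617. This exceeds 79 once k is above 79 × 0.0617/(2 × 7.85) = 0.31. Beyond that dispersion, no control rate gives 80% power for a 22% relative reduction. Below it, a high enough rate can.

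**Step 4. Why the window matters.** If 3.65 is a 24-month mean, the 12-month mean is 1.83, and power at 79 per group is about 51% even with k = 0.

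**Step 5. Type I error if independence enters the model.** With no treatment effect, Poisson standard errors are too small by √(1 + k·m1), and the true two-sided error is 2[1 − Φ(1.96/√(1 + k·m1))]. At m1 = 3.65:

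- k = 0.2: factor 1.32, error 14%.
- k = 0.5: factor 1.68, error 24%.
- k = 1.0: factor 2.16, error 36%.

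Simulation of 20,000 null trials gave 13.5%, 24.1% and 36.1%. With 12-month counts (mean 1.83) the formula gives 9%, 16% and 24%.

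**The case against.** The strongest reply is that the document does not show how 79 was obtained. The control rate comes from cited studies that are not at hand. The same 79 arises with some between-patient variation (k = 0.1 and 5.4 control events), or from a two-proportion test, where independence of repeat events plays no part. A reader might infer that 79 per group flatly fails to give 80% power. The document does not support that, because the loss is conditional on route, rate and dispersion. The two-proportion route is no rescue, however, since the calculation then powers a proportion and not the declared count.

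A reader might also infer that the planned standard errors are too narrow. That is not supported either. The analysis section names no Poisson model, a regression adapted to count data may well be negative binomial, assumptions are to be checked, and adjustment for exacerbation history absorbs part of the variation. Even so, a residual k of only 0.1 on the Poisson route leaves power at 68%.

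The independence clause could be read as a counting rule, each new episode being a separate event. If so, it should say that. The figure on 10% of patients concerns costs, not counts, so it is indirect evidence; the described decline is the more direct conflict.

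Silence about a time offset is detail that an article may leave to the analysis plan. A bias from unequal drop-out cannot be asserted, because only a 20% overall rate is stated. Neither is counted as a fault here.

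**Conclusion.** The point holds in conditional form. The independence assumption is explicit, is attached to a recurrent count within patients, and conflicts with the protocol's own account of frequent exacerbators. The sample size section shows nothing that allows for differences between patients. On the relative Poisson route (RR 0.78, about 3.65 control events), the stated 80% power becomes about 59%, 41% and 28% at k = 0.2, 0.5 and 1.0. On the two-proportion route, the stated power belongs to another outcome. The k values and the 3.65 are assumptions, not figures from the document. Type I error of 14% to 36% is a risk only if independence is carried into an uncorrected Poisson model.

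**What to change.** 1. Delete the independence assumption from *Primary outcome measure*. If a counting rule was meant, state it as one.
2. Specify negative binomial regression for the primary count, or quasi-Poisson or robust standard errors. Preferably use log time observed as offset and the two stratification factors (exacerbation severity and GOLD stage) as covariates.
3. Restate *Size of the study population* with the control rate, the window, whether 22% is relative, and a range of dispersion. Alternatively, keep 79 per group and give the detectable rate reduction, with the assumed control rate beside it.

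The cost is a change of wording and a less favourable stated power. No extra patients or data are requested.
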